## Abstract

**Background::**

Chronic low back pain is one of the major conditions causing serious personal and social difficulties in modern society. There are several noninvasive therapies for chronic low back pain; however, the effects of electromagnetic acupuncture have not been studied. Here, we describe the protocol for a study that will investigate the efficacy and safety of electromagnetic acupuncture for patients with chronic low back pain.

**Methods::**

The study has been designed as a double-blind, single-center, parallel-arm, sham-controlled, randomized clinical trial. A total of 104 patients with chronic low back pain who meet the criteria for selection and exclusion will be enrolled in a 1:1 ratio in an electromagnetic acupuncture group or a sham group. Sterilized disposable needles will be inserted at 6 acupoints, following which stimulation via an electromagnetic (Whata153) or a placebo (sham) stimulator will be applied. The 2 groups will receive a total of 6 treatment sessions over 3 weeks, with 1 follow-up visit within 3 days after the final treatment. The primary outcome will be the change in the visual analog scale (VAS) score for pain from baseline (visit 1, first treatment session) to the follow-up visit (visit 7, after treatment completion). The secondary outcomes will be as follows: changes in the VAS score for pain from baseline (visit 1) to visits 3 (third session) and 5 (fifth session); changes in the VAS score for pain at all assessment points from baseline (visit 1) to the follow-up visit (visit 7); changes in the Oswestry Disability Index (ODI) from visit 1 to visits 3, 5, and 7; and the change in ODI at all assessment points from visit 1 to visit 7.

**Discussion::**

The results of this trial are expected to provide important clinical information on the efficacy and safety of electromagnetic acupuncture for patients with chronic low back pain.

## Introduction

1

Chronic low back pain is one of the major conditions causing severe personal and social difficulties in modern society. Nonspecific chronic low back pain refers to pain that lasts for at least 3 months without a pathological anatomical abnormality.^[1]^ Most Americans have experienced low back pain, and approximately a quarter of adults investigated have reported low back pain lasting for a minimum of 1 day in the past 3 months.^[2]^

The Guidelines for Chronic Back Pain of the American College of Medicine, published in 2017, emphasize the importance of nonpharmacological treatment. According to these guidelines, nonsteroidal anti-inflammatory drugs (NSAIDs) and muscle relaxants can be considered if symptoms do not improve after nonpharmacological treatment, such as acupuncture and physiotherapy. Tramadol or duloxeine can be considered if NSAIDs and muscle relaxants are ineffective. Therefore, the demand for oriental medicine treatment for chronic low back pain has been increasing of late.^[3]^

According to the Survey on the Use of Oriental Medicine by the Korean Ministry of Health and Welfare in 2017, 73.8% of Koreans overall use oriental medicine. Low back pain was the most common symptom, accounting for 52.7% of cases. More specifically, acupuncture, cupping, moxibustion, and oriental physiotherapy were used for 90.2%, 53.0%, 49.1%, and 40.2% cases, respectively.^[4]^

Low-frequency electroacupuncture is used to control pain and muscle tension. Many studies have shown that electroacupuncture has a better effect on low back pain than does conventional acupuncture.^[5–7]^ Some studies have also evaluated electromagnetic acupuncture, a less-commonly used modality, for muscle fatigue recovery, meridian potential changes, and activation of the autonomic nervous system.^[8,9]^

Electromagnetic stimulation is based on the following principle. When a magnetic field is applied to a human body, a new electric field and electric current are generated, and the ions electrically stimulate the surrounding nerves. The intensity of the electric field decreases as it penetrates the skin. The advantage of electromagnetic stimulation is that the loss of the electric field in the skin is much less than that associated with electrical stimulation. For example, using the same intensity of stimulation of the skin, electromagnetic stimulation induces an electric field that is 10 times higher than that induced by electrical stimulation in a nerve located within 40 mm of the skin.^[10]^ Because the intensity of stimulation required to produce the same effect is lower with electromagnetic stimulation than with electrical stimulation, patients experience less discomfort and pain and may experience more positive effects with the former than with the latter.

Electromagnetic acupuncture may therefore also be effective in relieving chronic back pain; however, few studies have validated this. When an electric current is applied to a coil that is wound into a cylindrical shape, a magnetic field is produced. When an acupuncture needle, which is a magnetic substance, is inserted into the coil, an electromagnet is formed and a stronger magnetic field is achieved.

We aim to investigate the efficacy and safety of electromagnetic acupuncture in patients with chronic low back pain and to collect the relevant data. Here, we describe the protocol for a parallel-arm, sham-controlled, randomized clinical trial for evaluating the efficacy and safety of electromagnetic acupuncture for patients with chronic low back pain. We intend to use the Whata153 (Medi Lab., Korea), a device that converts electric energy into magnetic energy, for electromagnetic stimulation.

## Methods

2

### Study design

2.1

This study has been designed as a double-blind, single-center, parallel-arm, sham-controlled, randomized clinical trial for investigating the efficacy and safety of electromagnetic acupuncture for treatment of patients with chronic low back pain.

A total of 104 patients with chronic low back pain who meet the criteria for selection and exclusion will be enrolled in a 1:1 ratio, with 52 patients included in an electromagnetic acupuncture group (EMA group) and 52 in a sham group.

### Ethics approval

2.2

The study protocol has been approved by the Institutional Review Board of Cheonan Korean Medicine Hospital, Daejeon University (protocol number: M2015-01-1). The protocol was registered with Korean National Clinical Trial Registry CRIS (KCT0002915). The protocol accords with the Declaration of Helsinki.

### Participants

2.3

#### Inclusion criteria

2.3.1

The inclusion criteria are as follows: age, 19 to 70 years; presence of chronic low back pain for >3 months; a minimum pain intensity score of 40 mm on a 100-mm visual analog scale (VAS); ability of the participant to fully understand the trial procedure and the risks involved, communicate with the examiner, and comply with the protocol; and provision of written informed consent for participation.

#### Exclusion criteria

2.3.2

The exclusion criteria are as follows: a history of spinal surgery; progressive neurological deficit or severe psychiatric or psychological disorders; serious spinal disorders, such as metastatic cancer, vertebral fracture, spinal infection, and inflammatory spondylitis; other contraindications for treatment, such as clotting disorders, use of anticoagulants, and seizure disorders; presence of a device that could be affected by electromagnetic fields, such as a pacemaker or a hearing aid; use of medications that could affect the trial results, such as corticosteroids and anticonvulsants, within the last week; pregnancy, lactation, or plans for conception; participation in other clinical trials; and ineligibility judged by a physician.

### Procedures

2.4

Patients with chronic low back pain will be recruited through advertisements on hospital bulletin boards and websites. Individuals interested in participating will be provided an explanation of the study until they have completely understood the risks and benefits. If they agree to participate, they will be asked to sign a consent form and undergo screening for eligibility. If they are found to be eligible, a study researcher will randomly allocate them to either the treatment or the sham group. The treatment procedure will be scheduled after randomization. The study flow chart is presented in Fig. 1.

**Figure 1 F1:**
[figure not shown]
Study flow chart.

### Randomization and blinding procedures

2.5

The block randomization method will be used for randomization, at a 1:1 ratio, to ensure balanced distribution. The random assignment code will be calculated using a computer software program, and statisticians will assign codes according to the randomized lists. The randomization code will be sealed in an opaque envelope and stored at the hospital.

The patients and researchers performing treatment or assessing outcomes will be blinded to the treatment. To ensure blinding, needles for both groups will be manufactured in the same size and package. The Whata153 will be used for electromagnetic stimulation in the EMA group. In the sham group, a placebo stimulator with the same shape, sound, and machine motion will be used. The patients will not be able to identify the treatment, because the skin receives almost no sensory stimulus with electromagnetic stimulation.

Randomization and blinding are not disclosed to the investigator until the end of the clinical trial, except for disclosure to individual patients in an emergency.

### Interventions

2.6

Both the EMA and sham groups will receive a total of 6 treatment sessions over 3 weeks, with 1 follow-up visit within 3 days after the last treatment (end of the clinical trial). The trial will be conducted under the same conditions for all participants, and the same practitioners will treat all participants. Other therapies and treatments associated with chronic low back pain will be excluded during the trial period. Use of medications other than those specified in the exclusion criteria (e.g., steroids, anticonvulsants) will be maintained. The acupuncture protocol to be used is based on the Standards for Reporting Interventions in Clinical Trials of Acupuncture (STRICTA) and is presented in Table 1.

**Table 1 T1:**
[figure not shown]
Electromagnetic acupuncture protocol, based on the Standards for Reporting Interventions in Clinical Trials of Acupuncture, for patients with chronic low back pain.

### Acupuncture treatment

2.7

The bilateral BL23, BL24, and BL25 acupoints, which are frequently used for chronic low back pain, have been selected in accordance with previous studies^[11,12]^ (Fig. 2). Sterilized disposable needles measuring 0.3 × 40 mm in size (DB9; Dongbang-Medical, Sungnam, Korea) will be inserted at the 6 acupoints. After the needle is inserted, the Whata153 (EMA group) or a placebo stimulator (sham group) will be applied as follows. The ring in which the electromagnetic field is generated will be placed around the needle (Fig. 3). Stimulation lasting approximately 20 minutes in the E6 settling mode (500 Hz, interference wave) will then be applied.

**Figure 2 F2:**
[figure not shown]
Location of acupoints used for treatment of chronic low back pain.

**Figure 3 F3:**
[figure not shown]
The Whata153 (A), which is an electromagnetic acupuncture device, and a diagram illustrating the process of electromagnetic acupuncture (B).

### Acupuncturists

2.8

Licensed Korean Medicine doctors with more than 2 years of clinical experience will perform the treatment procedures. All acupuncturists and researchers will strictly comply with the study protocol and complete the training program.

### Data collection

2.9

During the screening period, the participants will complete a questionnaire regarding their sociodemographic characteristics, provide their medical history, undergo a physical examination in the lumbar region, and rate their pain using the VAS.

Personal information and data collected during the screening period will be shared and managed by the hospital. As the researchers are clinical, a data monitoring committee is not needed. The final trial dataset is accessible to statisticians and principal investigator.

The schedule for treatment and outcome measurements is presented in Table 2. Visits 1 to 6 will include the treatment sessions, while visit 7 will be the follow-up visit after treatment completion.

**Table 2 T2:**

Schedule for treatment (electromagnetic acupuncture or placebo) and outcome measurements for patients with chronic low back pain.

### Outcome measurements

2.10

The primary and secondary outcomes will be based on the VAS score for pain and the Oswestry Disability Index (ODI). The VAS has been shown to be a reliable tool for evaluating chronic pain.^[13]^ VAS for pain is a continuous scale with a horizontal or vertical line measuring 100 mm in length.^[14]^ Patients rate their current pain intensity from 0 (no pain) to 100 (worst pain imaginable).^[15]^ ODI was developed as a patient-oriented assessment tool and includes various questions that are answered by the patients themselves.^[16]^ The score is calculated as the total score/(number of questions provided by the author ∗ 5) ∗ 100.

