#### Secondary outcomes

2.10.2

The following will be assessed as secondary outcomes: changes in the VAS score for pain from baseline (visit 1) to visits 3 (third session) and 5 (fifth session); changes in the VAS score for pain at all assessment points from baseline (visit 1) to the follow-up visit (visit 7); changes in the ODI from visit 1 to visits 3, 5, and 7; and the change in ODI at all assessment points from visit 1 to visit 7.

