### Sample size

2.13

The sample size will be calculated as per the results of previous trials on electroacupuncture therapy for chronic low back pain, because there are no available studies on electromagnetic acupuncture therapy. We assume that the effect of electromagnetic acupuncture would at least be equivalent to those of electroacupuncture; therefore, we will refer to the effect size of electroacupuncture therapy as conservative treatment for low back pain. In a previous study, the mean difference in the follow-up VAS score for pain was 0.87 between groups, with an estimated standard deviation of 1.48.^[17]^ The alpha level is 5% for both sides, and the study power is maintained at 80%. A total of 52 participants will thus be required in each group after considering an attrition rate of 10%.

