### Statistical analysis

2.14

Statistical analysis will be primarily based on the intent-to-treat principle, although per-protocol principles will also be checked. The missing values will be analyzed by the last observation carried forward method. The significance level will be set at *P* < .05, and the confidence interval at 95%. All statistical analyses will be performed using SPSS Statistics for Windows Version 20.0 (IBM Corp., Armonk, NY). There is no intermediate analysis of this study, and the final decision on end of trial is with principal investigator.

Differences in sociodemographic and baseline characteristics between the EMA and sham groups will be evaluated. For continuous data, Student *t* test or the Wilcoxon rank sum test will be performed. For categorical data, the Chi-square test or Fisher exact test will be used.

Changes in VAS and ODI scores from baseline to each assessment point will be assessed using Student *t* test or the Wilcoxon rank sum test, while those at all evaluation points from baseline to the follow-up visit will be assessed using repeated measures analysis of variance (RM-ANOVA). The incidence of adverse events will be investigated using the Chi-square test or Fisher exact test.

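### As printed, the ODI formula divides by the questions provided, so a skipped item on a partly completed form would be scored like a zero unless items are imputed

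*Protocol article*

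**What the plan says.** The protocol article, Outcome measurements (2.10), describes the ODI as an instrument that "includes various questions that are answered by the patients themselves". It then gives the scoring rule in full: "The score is calculated as the total score/(number of questions provided by the author", with that number multiplied by 5 and the resulting ratio multiplied by 100. It does not say how many questions the form has, who the author in that phrase is, or how a blank question is treated.

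Secondary outcomes (2.10.2) builds on this score: "changes in the ODI from visit 1 to visits 3, 5, and 7", plus an analysis of all assessment points together. The primary outcome is the pain VAS, which this formula does not touch.

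On missing data, Statistical analysis (2.14) says only: "The missing values will be analyzed by the last observation carried forward method". It does not say whether this covers single questionnaire items or whole scores.

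**The concern.** A percentage score of this kind compares points scored with points obtainable. If the obtainable points are counted over every question on the form, a question the patient left blank contributes 0 above the line and 5 below it, exactly as if the patient had reported no limitation. Patients complete the form themselves, so blanks are possible.

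The article prints a scoring rule here, so this is not a matter of detail left to a fuller document. A programmer who followed the printed rule would code a fixed denominator. Every ODI outcome is a change from visit 1, so a blank at one visit but not the other would register as a change in a patient whose disability had not moved. What is at stake is the accuracy of the secondary disability results.

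**Working it through.** **Inputs from the protocol article.** Formula: total score / (questions provided × 5) × 100 (2.10). Self-completed form (2.10). ODI changes from visit 1 to visits 3, 5 and 7 (2.10.2). Last observation carried forward (LOCF), level unstated (2.14).

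**Assumptions, not in the document.** The form has 10 items, each scored 0 to 5. Skipped items resemble the answered ones. Single items are not imputed.

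**The plan's own figure.** The article gives no worked ODI score to reproduce. Its one derived figure is the sample size, based on the VAS: difference 0.87, SD 1.48, two-sided 5%, power 80%, 10% attrition. This gives n = 2 × (1.960 + 0.842)² × 1.48² / 0.87² = 45.4, rounded up to 46. Then 46 / 0.90 = 51.1, rounded up to 52 per group, as stated. A t-based calculation gives 47 before attrition and 53 after it, which is close enough. The ODI formula does not enter it.

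**One form, two denominators.** Take a patient who averages 2 points per item and leaves one of 10 items blank. The total is 9 × 2 = 18.

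- Questions provided: 18 / (10 × 5) × 100 = 36.
- Questions answered: 18 / (9 × 5) × 100 = 40, the same as the complete form, 20 / 50 × 100 = 40.

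**General size.** With k of 10 items skipped and mean item score m, the fixed denominator gives (10 − k) × m / 50 × 100, against a true score of 10 × m / 50 × 100. The shortfall is k/10 of the true score.

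| True score | Fixed denominator, 1 skipped | Shortfall | Fixed denominator, 2 skipped | Shortfall |
|---|---|---|---|---|
| 20 | 18 | 2 | 16 | 4 |
| 40 | 36 | 4 | 32 | 8 |
| 60 | 54 | 6 | 48 | 12 |
| 80 | 72 | 8 | 64 | 16 |

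**Direction.** For an unchanged patient at 40 with one skip, a blank at visit 7 only gives 36 − 40 = −4, a false improvement. A blank at visit 1 only gives 40 − 36 = +4, a false worsening.

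**Effect on the comparison of arms.** Suppose true follow-up means of 40 and 35, complete forms at visit 1, and the same proportional loss in both arms at follow-up (all assumed). With a 5% loss the difference is 5 × 0.95 = 4.75, a shrinkage of 0.25 points. With a 10% loss it is 5 × 0.90 = 4.50, a shrinkage of 0.5 points. One skip costs 10% of a score, so a 10% average loss would need every patient to skip one item. A 5% loss would need half of them to, if skipping is unrelated to score. Bias towards one arm needs skipping that differs between the arms.

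**The case against.** The strongest reply is that the wording is too unclear to prove a wrong formula. The author in the phrase is undefined. It could be the developer of the instrument or the person filling in the form, and the expression may be a garbled reference to items answered by the respondent. A fixed denominator could also have been printed simply as a number. This stands as far as intent goes: the article does not firmly establish that its authors mean to divide by items provided. It does not rescue the text, because nothing elsewhere supplies the answered-items reading and the literal one is what would be programmed.

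A second reply is that LOCF might be applied item by item. The article does not exclude this. An item answered at visit 1 and blank at visit 7 would then take its earlier value, and the false improvement would disappear. So it cannot be said that every skipped item is scored as zero. But the article does not state item-level LOCF either. Under the printed formula a partly completed form still yields a score, so score-level LOCF would not be triggered. Nor could item-level LOCF fill a blank at visit 1, since the text describes no earlier ODI.

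Third, counting only answered items is itself an assumption about the blanks, and the source cited for the instrument is not available here. That is fair, and it is a cost of the fix. A rule for the minimum number of answered items is detail that an article may leave to the full protocol, so its absence is not criticised.

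A reader might also infer that the formula inflates the treatment effect. The documents do not support that. The error runs in both directions, the arms are blinded, and nothing suggests that one arm would skip more.

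**Conclusion.** The point holds in a limited form. The printed denominator, taken literally, treats a blank item like a zero on any partly completed form, unless item-level imputation is applied. On 10 assumed items, with skipped items similar to answered ones, each skip moves a patient's score by a tenth of its value, with the sign depending on the visit at which the item is skipped. No skip rate is given, so the total effect on the trial cannot be sized. Under equal skipping in both arms, the illustration above puts the distortion of a 5-point difference at half a point or less.

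The primary VAS outcome and the sample size are untouched, and complete forms score the same either way. This is a scoring rule to correct before the ODI is programmed. It is not a threat to the trial's main conclusion, and it is not proof that the authors intended a fixed denominator.

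**What to change.** In Outcome measurements, replace the formula with: total score / (number of questions answered by the patient × 5) × 100, applied identically at visits 1, 3, 5 and 7. In Statistical analysis, state that for the ODI, last observation carried forward applies to the whole score and not to single items, so that blanks are not handled twice.

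The cost is one corrected formula, one clarifying sentence and one line of scoring code, with no change for sites, patients or sample size. The small downside is that prorating assumes skipped items resemble the answered ones, which the text should say.

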#### Primary outcomes

2.10.1

The change in the VAS score for pain from baseline (visit 1, first treatment session) to the follow-up visit after treatment completion (visit 7) will be assessed as the primary outcome.

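### The primary VAS analysis is an unadjusted change from one momentary visit-1 rating and leaves the screening VAS unused; entering both ratings as covariates would gain precision at almost no cost.

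*Protocol article*

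**What the plan says.** Section 2.10.1 sets the primary outcome as "The change in the VAS score for pain from baseline (visit 1, first treatment session") to visit 7, and the abstract agrees. Section 2.10.2 takes the secondary VAS changes from the same visit-1 value. Section 2.10 makes the rating momentary: "Patients rate their current pain intensity from 0 (no pain) to 100 (worst pain imaginable").

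Section 2.9 has patients "undergo a physical examination in the lumbar region, and rate their pain using the VAS" during screening, and section 2.3.1 requires at least 40 mm for entry. Section 2.4 places screening before randomisation and adds: "The treatment procedure will be scheduled after randomization". Sections 2.10 to 2.14 give the screening value no role.

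Section 2.14 compares changes to each visit by Student t test or Wilcoxon rank-sum test, and the all-visit data by repeated-measures ANOVA. It names no baseline covariate. On planning, section 2.13 says "The alpha level is 5% for both sides" and "the study power is maintained at 80" per cent.

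**The concern.** Pain that has lasted more than 3 months fluctuates, and a single rating of pain at the moment is a noisy measure of it. In a raw change score that noise is subtracted in full. A covariate model instead weights the visit-1 rating by how well it predicts visit 7, and a second untreated rating can add to that prediction. The planned analysis does neither, although the screening rating will already be in the database. At stake is the standard error of the primary arm difference in a trial planned at 80% power. The validity of the comparison is not at stake.

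**Working it through.** **1. The plan's own figure.** Inputs from section 2.13: "the mean difference in the follow-up VAS score for pain was 0.87 between groups, with an estimated standard deviation of 1.48", two-sided alpha 0.05, power 80%, attrition 10%.

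n per arm = 2(1.960 + 0.842)² × 1.48² / 0.87² = 45.4, so 46; 46 / 0.9 = 51.1, so 52. This matches: "A total of 52 participants will thus be required in each group after considering an attrition rate of 10" per cent. The stated size reproduces and does not depend on the choice of baseline.

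**2. Assumptions.** The article gives no correlations between repeated VAS ratings. Write r_s1 for screening with visit 1, r_17 for visit 1 with visit 7, and r_s7 for screening with visit 7, with equal SDs. Assume that the visit-1 rating precedes the first needling, that screening is on another day, and that the 40-mm rule is applied to the screening rating.

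**3. Adjusting for visit-1 VAS alone.** In units of the score variance, the raw change has variance 2(1 − r_17). The model with visit-1 VAS has residual variance 1 − r_17². The ratio is (1 + r_17)/2, that is 0.70, 0.75, 0.80 and 0.85 at r_17 = 0.4, 0.5, 0.6 and 0.7. The variance therefore falls by 15-30% without any use of screening VAS.

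**4. Adding screening VAS, equal correlations.** Simulation with mean 55 mm, SD 20 mm and patients kept only if screening VAS is at least 40 mm:

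| Common correlation | Residual variance, both covariates ÷ visit 1 only | Further reduction |
|---|---|---|
| 0.4 | 0.950 | 5% |
| 0.5 | 0.927 | 7% |
| 0.6 | 0.902 | 10% |
| 0.7 | 0.874 | 13% |

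At 0.5 the variances in mm² are: change from visit 1, 399; change from the mean of the two ratings, 288; model with visit 1, 287; model with both, 266. Of the total drop of 399 − 266 = 133, visit-1 adjustment supplies 399 − 287 = 112, or 84%.

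In patients, with 104 × 0.9 = 93.6 evaluable, the further reduction is worth 93.6 × (1/0.950 − 1) ≈ 5 to 93.6 × (1/0.874 − 1) ≈ 13 patients in total.

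**5. Adding screening VAS, unequal correlations.** The further proportional reduction is (r_s7 − r_s1·r_17)² / [(1 − r_s1²)(1 − r_17²)], before the 40-mm cut-off:

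| r_s1, r_17, r_s7 | Calculation | Further reduction |
|---|---|---|
| 0.7, 0.5, 0.4 | 0.05² / (0.51 × 0.75) | 0.7% |
| 0.8, 0.5, 0.4 | 0² / (0.36 × 0.75) | 0 |
| 0.8, 0.7, 0.5 | 0.06² / (0.36 × 0.51) | 2.0% |

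With the cut-off applied these become about 0-1.5%. In the same three cases the two-covariate model still has 0.78, 0.81 and 0.89 of the variance of the planned change, nearly all of it owed to visit-1 VAS.

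**6. Averaging the two ratings as the baseline.** The variance ratio to the planned change is [1 + (1 + r_s1)/2 − r_17 − r_s7] / [2(1 − r_17)]. It is below 1 only if r_s1 < 1 − 2(r_17 − r_s7). With equal correlations it is 0.75. At (0.8, 0.7, 0.5) it is 0.70/0.60 = 1.17, a loss. In simulations with equal correlations of 0.3-0.7, population means of 50-60 mm and SDs of 15-20 mm, the 40-mm cut-off made the averaged baseline show a spurious within-arm fall of about 0.4-3.6 mm, against about 0 from visit 1.

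**The case against.** The best defence is that nothing here is an error. A baseline tied to the first treatment session, and kept apart from the score that qualified the patient, is conventional and has a purpose, because the qualifying score is selected upward. The article uses it consistently. That stands, and it is why visit 1 should remain the reported baseline.

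A second defence is that covariates are usually left to an analysis plan that is not shown. This carries less weight here, because the article itself fixes both the baseline and the unadjusted tests.

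A third is that two separate untreated ratings are not proven. The contents of Table 2 are not available, and the wording on scheduling after randomisation suggests a later visit without giving an interval. That also stands: with both ratings on the same occasion, the gain from screening VAS is nil.

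A reader might go further and infer that leaving out screening VAS costs some 27-28% of the variance, or the difference between 80% and about 90% power. The documents do not support that. Those figures compare an averaged baseline with the unadjusted change under equal correlations, and at a correlation of 0.5 visit-1 adjustment alone does as well (287 against 288). The power figure also reads 1.48 as the SD of a change, whereas section 2.13 gives it alongside a difference in the follow-up score.

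**Conclusion.** The point holds as a modest, nearly free improvement in efficiency. The planned unadjusted change makes weak use of the visit-1 rating and none of the screening rating. Adjusting for visit-1 VAS supplies most of the gain. Screening VAS adds about 5-13% lower residual variance under equal correlations of 0.4-0.7, about 0-2% if it predicts visit 7 less well than visit 1 does, and nothing if the two ratings share an occasion. All these sizes rest on assumed correlations.

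It would be wrong to infer that the trial is undersized or the arm comparison biased. The 52 per arm reproduces, and the randomised comparison is valid with or without the covariates. Because screening VAS precedes randomisation, entering it cannot bias that comparison, and the 40-mm cut-off applies to both arms alike.

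**What to change.** Keep visit 1 as the reported baseline. In section 2.14, state that visit-7 VAS will be compared between arms in a linear model with visit-1 VAS and screening VAS as covariates. With visit-1 VAS in the model, the arm difference is the same whether the response is visit-7 VAS or the change from visit 1, so the primary outcome need not be redefined. Use the same two covariates for the visit-3, visit-5 and all-visit VAS analyses. Settle this before unblinding, since covariates chosen afterwards would be open to challenge.

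The cost is one sentence, one already collected variable in the analysis dataset, and about one degree of freedom for the added covariate. The sample size need not change. Do not substitute the mean of screening and visit-1 VAS for the baseline, for the reasons in step 6 of the working.
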